### Monitoring

Patient data will be handled confidentially and in compliance with the Dutch Personal Data Protection Act. Collected data will be stored in Castor EDC, an electronic data capture program. Stored data will be coded, using a unique combination for centre and successive study number. The key to the code will be accessible by the local investigators and the coordinating investigators. Study data will be kept for 15 years and destroyed afterwards. The local investigators will have access to the link between code and personal data of the patients of only his centre. The coordinating and the principal investigator have access to all the data. The co-investigators will have access to the coded data of all patients.

The coordinating investigators will report all adverse events to the accredited Medical Research Ethics Committee (MREC) that approved the protocol. No data safety managing board is installed. The investigator will submit a summary of the progress of the trial to the accredited MREC once a year. Information will be provided on the date of inclusion of the first subject, numbers of subjects included and numbers of subjects that have completed the trial, serious adverse events/ serious adverse reactions, other problems, and amendments. No planned interim analyses will be conducted.

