### Study procedures

A time schedule of procedures and measurements is presented in Table 1. The selection of eligible patients will take place in the emergency department (ED). According to standard care, X-ray examinations of the pelvis and hip are made on admission and assessed by the radiologist and trauma surgeon. Eligible patients will receive oral and written information about the study from the physician in the ED. The patients have at least 6 h to consider participation in the study and will be given the opportunity to ask questions about the study. Written informed consent will be obtained by the surgical resident or the surgeon after admission to the ward. Randomization will be done by the treating surgeon. After inclusion the patient will be allocated to one of the two study groups (DLBP or DHS) using an online randomization program. The baseline parameters will be registered by a nurse upon arrival on the surgical ward before surgery. The perioperative care will be the same for all included patients.

**Table 1 Tab1:** Time schedule for study procedures and measurements

	Emergency department	Admission	Post-op visit (≤5 days)	6 weeks follow-up	3 months follow-up	6 months follow-up	12 months follow-up	24 months follow-up^a^
Informed consent		x						
Baseline characteristics		x						
Radiography	x		x	x	x		x	
Questionnaires		x		x	x	x	x	x
Complications registration		x	x	x	x		x	x

^a^ Contact by telephone

Surgery will be performed by an (orthopaedic) trauma surgeon or by an (orthopaedic) trauma resident under the direct supervision of an (orthopaedic) trauma surgeon. The aim is to operate within 24–36 h based on the Dutch guidelines for treatment of FNFs [18]. After surgery, details about the surgery will be documented.

After discharge patients are scheduled for outpatient visits after 6 weeks, 3 and 12 months. Conventional radiographs will be taken and assessed during these visits (Table 1). The patients need to fill out a questionnaire before follow up visits and 6 months after discharge. Also, the patient will be contacted by telephone 24 months after enrolment in the study for additional questionnaires about mobility and complication registration.

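### Co-investigators may see all patients' coded records with no stated limit by arm or time, so the running revision rate by implant is open to any of them who also recruits, operates or assesses outcomes

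*Protocol article*

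**What the plan says.** The Monitoring section of the protocol article sets out who may see what:

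- Co-investigators: "The co-investigators will have access to the coded data of all patients".
- Lead investigators: "The coordinating and the principal investigator have access to all the data".
- Local investigators: "The local investigators will have access to the link between code and personal data of the patients of only his centre".
- What coding means: "Stored data will be coded, using a unique combination for centre and successive study number".

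The same section states that no interim analysis is planned and that "No data safety managing board is installed". It also provides for outside reporting: "The coordinating investigators will report all adverse events to the accredited Medical Research Ethics Committee (MREC) that approved the protocol". A yearly progress summary goes to the same committee.

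Elsewhere, Study design calls the trial unblinded. Study procedures says "Randomization will be done by the treating surgeon". Primary outcome parameter defines the endpoint as revision for non-union, AVN or cut-out over 1 year. Secondary outcome parameters makes the treating surgeon the assessor of both AVN and non-union.

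**The concern.** The access rules protect patients' identity but leave the accumulating comparison open. The only own-centre limit concerns the link to personal data. Nothing stated keeps outcome records from other centres away from people who may be treating trial patients.

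This matters because the endpoint is a decision to reoperate. A surgeon who knows only the local patients has a handful of cases for each implant. A surgeon who can read all centres' records knows the trend of the trial. That knowledge can change the threshold for revising a doubtful hip, the willingness to offer the trial to the next patient, and the willingness to keep to the allocated implant. A plan without interim analyses normally relies on nobody involved in care knowing that trend.

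**Working it through.** The point concerns access and rests on no disputed figure, so most of the check sets the provisions side by side.

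1. **Does coding hide the implant?** No. Monitoring describes the code as a combination of centre and study number, which is pseudonymisation. Study design says the trial is unblinded. Surgical details are recorded after the operation (Study procedures), and the implant-related complication definition includes faults of the anchors, which the article describes only for the DLBP. It is an inference, but a safe one, that a coded record shows which implant the patient received.

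2. **Is access limited by time or centre?** Not for co-investigators. The sentence covers all patients and mentions no lock date. The limit for local investigators applies to the identity link.

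3. **Can the endpoint respond to knowledge of the trend?** Yes. AVN and non-union, two of the three reasons for a primary-endpoint revision, are judged by the treating surgeon. Non-union normally needs at least 9 months. It may be declared sooner if revision was done because healing was no longer expected, so the decision to revise can itself help to complete the definition. The treating surgeon also randomises.

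4. **How many decisions does the comparison rest on?** Inputs from Sample size calculation: 30% (DHS), 15% (DLBP), 121 per group for analysis, 133 per group included.
   - With 121 per group: 121 × 0.30 = 36.3 and 121 × 0.15 = 18.2, about 54 revisions in all.
   - With 133 per group: 133 × 0.30 = 39.9 and 133 × 0.15 = 20.0, about 60 in all.
   - One revision moves an arm's rate by 1/133 = 0.75 to 1/121 = 0.83 percentage points.

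   These figures show that the trend rests on few events and is easy to count from a record list. They do not estimate any bias.

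5. **Does the point touch the design figures?** No. The usual two-proportion formula (pooled variance, no continuity correction, two-sided 5%, 80% power, 30% versus 15%) gives 121 per group, as stated, with power 80.2%. Restricting access changes neither the sample size nor alpha.

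**The case against.** The strongest reply has four parts.

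- **Context.** The sentence closes a paragraph on privacy, where its job is to separate coded from identifiable data. Time-based or role-based database permissions usually sit in a full protocol or data management plan, which is not shown. This stands in part: a limit may exist elsewhere. But the point rests on a grant of access that the article makes without qualification, not only on silence. If a limit exists, the sentence needs a clause to say so.

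- **Roles.** The article never defines co-investigators or says that they operate. This stands, and the point is therefore conditional: it concerns any co-investigator who also recruits, operates or assesses outcomes.

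- **Access is not analysis.** No interim analysis is planned, and being able to read records does not mean that anyone tabulates them. This also stands. The point is an avoidable opportunity for bias, not evidence that bias will occur.

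- **Lack of blinding already does the harm.** Surgeons know each patient's implant and may expect the DLBP to do better. That bias exists without pooled access and cannot be removed by database permissions. What pooled access adds is the trend across centres, and that part can be removed.

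A reader might go further and infer that, with no safety board, results are closed to everyone charged with safety. The document does not support this. The ethics committee receives all adverse events, and its yearly summary covers "numbers of subjects included and numbers of subjects that have completed the trial, serious adverse events/ serious adverse reactions, other problems, and amendments". What the article does not mention is a breakdown by implant; it does not say that the reports are masked to implant.

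**Conclusion.** The point holds in a limited form. As written, the article opens all patients' unmasked records to co-investigators during accrual, in an unblinded trial whose primary outcome is partly discretionary. That is an avoidable addition to the risk of bias and is cheap to remove.

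It rests on two assumptions: that some co-investigators recruit, operate or assess outcomes, and that no unshown document already restricts access before lock.

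Its size cannot be derived. A reader might move a few revisions from one arm to the other and quote the resulting inflation of the difference. Any such shift would be invented in both number and direction, and could not be separated from the bias that unblinded surgeons carry anyway. Nor is the stated alpha wrong: no repeated testing or early stopping is planned.

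**What to change.** Replace the access sentence in Monitoring with wording to this effect:

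- Until database lock, co-investigators and local investigators have access in Castor EDC only to the records of their own centre.
- Until database lock, nobody who recruits patients, operates or assesses outcomes may tabulate revision, AVN, non-union or implant-related complications by arm.
- The coordinating and principal investigators keep the trial-wide access needed to report adverse events to the ethics committee, under the same ban on tabulation by arm.

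Keeping trial-wide access for the lead investigators is deliberate, because limiting every investigator to one centre would obstruct the reporting duty in the same section. A yearly table of revisions by arm for the ethics committee is not part of this fix. It would be a repeated look at the primary outcome by a body not set up as a safety board, with no stopping guideline, and it would need an independent person to prepare it.

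The cost is a permission setting and a few lines of text. The small downside is that co-investigators lose pooled data until lock. Sample size, alpha and visits are unchanged.

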## Discussion

In this paper we present the rationale and design of a randomized controlled trial that compares the clinical outcomes of the DLBP and the DHS. The DHS is a globally accepted osteosynthesis and it has been for decades. Yet the failure rate is high. The DLBP is a new implant that is on the market since 2010. Today’s evidence for this implant is not as widespread as for the DHS, but the results from (non randomized) earlier studies are promising [13, 14]. The outcome of the DEFENDD trial will provide high-level evidence of which implant is favorable for the treatment of femoral neck fractures in young patients (≤65 years). The results of this trial will be published in peer-reviewed international journal.

## Data Availability

The datasets generated and/or analysed during the current study are not publicly available but are available from the corresponding author on reasonable request.

## Abbreviations

AVN: Avascular necrosis
BMI: Body mass index
DHS: Dynamic Hip Screw
DLBP: Dynamic Locking Blade Plate
ED: Emergency department
FNF: Femoral Neck Fractures
GCP: Good Clinical Practice
iHOT: International Hip Outcome Tool
MREC: Medical Research Ethics Committee
QALY: Quality Adjusted Life Years
RCT: Randomized Controlled Trial
WMO: Medical Research Involving Human Subjects Act (in Dutch: Wet Medisch-wetenschappelijk Onderzoek met Mensen)
